## Abstract

**Background:**

Shoulder function complications are common after treatment for breast cancer. Quite a few survivors still report a limited shoulder range of motion, even though the free range-of-motion upper limb exercise is helpful to restore shoulder function. Mirror therapy (MT) is a classical and effective rehabilitation technique to recover motor and sensory function for the limbs; in addition, studies have reported that MT has an influence on patients with shoulder functional dysfunction including increasing shoulder range of motion, improving shoulder function scores, and decreasing pain scores. Here, we describe a protocol of a randomized controlled trial to explore if free range-of-motion upper limb exercise based on MT has efficacy on shoulder function in survivors after surgery of breast cancer.

**Methods/design:**

This is a prospective, single-blind, two-arm randomized controlled trial. An estimated 70 participants will be randomly allocated to (1) the MT group or (2) the control group. The participants in the control group receive free range-of-motion upper limb exercise, and participants in the MT group will engage in free range-of-motion upper limb exercise based on MT. The intervention will start on the first day after surgery and be completed at 8 weeks after surgery. The primary outcome in this protocol is shoulder range of motion (ROM), while the Constant-Murley Score (CMS); Disability of the Arm, Shoulder, and Hand Questionnaire (DASH); Tampa Scale of Kinesiophobia (13-item TSK); visual analog scale (VAS); grip strength; arm circumference; and lymphedema are the secondary outcomes. Assessment will be conducted before allocation (baseline) and at 2 weeks, 4 weeks, and 8 weeks after surgery.

**Discussion:**

Based on the results that MT has an influence on shoulder function immediately after intervention in patients without nerve injury, this randomized controlled trial is to observe the efficacy of MT on shoulder function after a long-term intervention in breast cancer survivors. We look forward to the innovation of this study for both breast cancer rehabilitation and MT.

**Trial registration:**

Chinese Clinical Trial Registry (ChiCTR) ChiCTR2000033080. Registered on 19 May 2020

**Supplementary Information:**

The online version contains supplementary material available at 10.1186/s13063-021-05789-2.

## Background

Breast cancer is the most frequently diagnosed cancer among women throughout the world [1]; however, the 5-year survival for breast cancer is the highest among women’s cancer, and it is going up gradually [2]. Since both prevalence and survival rates continue to rise, breast cancer tends to become chronic. Similar to patients with chronic diseases, breast cancer survivors (BCS) have to fight the treatment-related complications that affect their health status and quality of life. Shoulder function complications are one of the most common sequelae following treatment for breast cancer, which can manifest soon after surgery or would appear many years later. Typical symptoms include a restricted shoulder range of motion (ROM), stiffness and weakness of the shoulder, and pain [3]. It is reported that there is a prevalence rate of 32.9% of a restricted shoulder ROM in patients at 1 year after axillary lymph node dissection and a prevalence rate of 23.2% in patients at 1 year after sentinel lymph node biopsy [4]. Pain and numbness are found to be 51.1% in BCS at 2 years after breast cancer surgery [5]. Shoulder function complications will adversely affect BCS in daily activity, medical burden, social life, and quality of life. It is limited to follow-up time; shoulder function complications persist much longer than it is reported in many studies. Hauerslev et al. reported that 25.7% and 30% BCS who are evaluated 11.7 years after surgery have decreased shoulder mobility and shoulder pain, respectively [6]. In the long run, shoulder function complications will damage the physical, psychosocial, and social domains of the function of BCS; thus, it is still a matter of concern.

Shoulder function complications of breast cancer are caused primarily by surgery, which causes damage and defect of soft tissues and myofascial restrictions on the upper body. In the effect of scar tissue formation, postsurgical pain, protective posturing, or breast reconstruction, chest wall soft tissue will become tight and short, losing their gliding ability that is relative to shoulder joint [3, 7–9]. Besides, radiotherapy probably causes soft tissue fibrosis and radiation dermatitis, leading to shoulder pain and dysfunction. Other complications such as wound complications, lymphedema, and axillary web syndrome, on the other hand, can also induce shoulder function complications [10–13].

Free range-of-motion upper limb exercise following breast cancer treatment can improve shoulder ROM and decrease chest tightness by moving and stretching the affected arm to restore shoulder joint flexibility and increase scar plasticity [14, 15]. Despite the fact that free range-of-motion upper limb exercise can improve long-term gains in shoulder function without increasing wound complications, there remains underutilization of free range-of-motion upper limb exercise, and quite a few BCS still have a restricted shoulder ROM and report shoulder pain even within 6 months after treatment [16, 17]. Many survivors fear movement after surgery because they fear that the affected arm will be injured. According to the cognitive model of fear of movement injury of Johan Vlaeye, individual fears of injury will lead to fear-avoid behaviors in daily activity [18]. Studies have reported that fear of being injured of the affected arm is one of the common barriers to underutilization of rehabilitation for BCS [16, 17].

Two prospective studies have suggested that mirror therapy (MT) may be a useful tool to improve shoulder function in patients with a restricted shoulder ROM and shoulder pain. MT is a classic rehabilitation therapy based on visual feedback of plane mirrored images. Along the midsagittal plane, placing a mirror between the two limbs, the affected limb is placed behind the mirror, and the unaffected limb faces the mirror. In this way, the reflection of the limb in front of the mirror is always superimposed on the limb hidden behind the mirror so that it could create a visual illusion of the health and intactness of the contralateral limb. When both upper/lower extremities move simultaneously, the individual is required to lean forward slightly to watch and concentrate on the complete reflection of the unaffected limb in the mirror and think the reflection is the move of the affected limb behind the mirror. MT is always a useful rehabilitation technique for patients with nerve injury, such as storks and phantom limb pain [18–21]. In addition, a few studies have reported that MT can improve limb motor function in patients without nerve injury. Altschuler and Hu reported a patient who has a fractured wrist, but no neurovascular impairment can extend her wrist actively after 10 weeks of MT intervention [22]. Rosen and Lundborg showed MT improved a woman’s finger active flexion, whose fingers were bit by a cat. In addition, a patient with rheumatoid arthritis gained good coordination and flexibility of the fingers after 8 weeks of MT intervention [23].

The details of MT intervention on the shoulder of two studies are as follows. Louw et al. asked the patients with shoulder pain and limited ROM to move their shoulder in front of a mirror 10 times for 3 mins; immediate assessment after intervention showed that shoulder flexion ROM has a mean increase of 14.5°, and pain levels averagely decreased to 0.48 [24]. Başkaya et al. conducted a two-arm randomized controlled trial of MT in patients with adhesive capsulitis; immediate measurement after intervention showed that shoulder ROM, VAS score, and the University of California-Los Angeles (UCLA) Shoulder Score of the experimental group improved obviously than that of the control group [25].

The potential mechanism of MT on motor function is using a mirrored image of the intact limb to compensate proprioceptive feedback to a motor command originated by the affected limb; in other words, MT normalizes the efference-afference loop of the sensorimotor brain circuits in a movement process [26, 27], in which, visual information primarily influence the proprioception. Studies in healthy individuals found the position of the hand in front of the mirror can influence the position of the hand behind the mirror. Louw and Başkaya measured the outcomes immediately after the intervention; the results of their studies only showed MT has an influence on shoulder movement. However, whether MT can improve shoulder function in a long-term intervention needs advanced study. Based on current studies, we are interested in the efficacy of MT on shoulder function in BCS. In addition, to our knowledge, no study has applied MT on shoulder function in BCS. What is more, MT has advantages of low cost, practicality, and easy-to-apply; if this trial provides expected results, MT will be expected to promote shoulder rehabilitation of BSC.

## Objectives

The purpose of this prospective, exploratory randomized controlled trial is that if free range-of-motion upper limb exercise based on MT will bring gains on efficacy compared with the effects of free range-of-motion upper limb exercise on shoulder function in patients after surgery of breast cancer. The main purposes of the trial are as follows:
Observing the efficacy of free range-of-motion upper limb exercise based on MT on shoulder ROM in BCSObserving the effects of free range-of-motion upper limb exercise based on MT on shoulder function score, shoulder pain, function, and disability of the upper limb in BCSObserving the effects of free range-of-motion upper limb exercise based on MT on fear of movement in BCS.

## Methods

### Study design

This is a prospective, single-blind, two-arm randomized controlled trial that will explore the effects of free range-of-motion upper limb exercise based on MT on shoulder function in patients after surgery of breast cancer. An estimated 70 participants from the galactophore department will be randomly allocated to (1) the MT group or (2) the control group. The control group is required to do free range-of-motion upper limb exercise, while the MT group engages in free range-of-motion upper limb exercise based on MT. An intervention team consisting of nurses, rehabilitation therapists, and surgeons will be set up. Outcomes will be measured at baseline and at 2 weeks, 4 weeks, and 8 weeks after the operation. Figure 1 shows the Recommendations for Intervention Trials (SPIRIT) flow diagram for this study.

**Fig. 1 Fig1:**
[figure not shown]
Recruitment and intervention processes flow chart

### Ethical

The ethical approval of this study was approved by the Ethical Committee of Longhua Hospital affiliated to the Shanghai University of Traditional Chinese Medicine on 5 May 2020 (reference number: 2020LCSY016). The research scheme, case report form, and informed consent form were approved by the Ethics Committee. Informed consent will be obtained from all participants before the intervention.

### Study setting

The study will be carried out at the galactophore department in the two hospitals in Shanghai, Longhua Hospital Shanghai University of Traditional Chinese Medicine and Fudan University Zhongshan Hospital. Outcome measurement will be conducted in a separate quiet room in the hospital.

#### Sample size

The primary outcome in this study is shoulder ROM, which is the main effect indicator for sample size estimating in this randomized controlled trial. Referring to Cohen’s effect size value of 1.3799 in the study of Başkaya et al. [25], to achieve 95% power and 0.05 error range, 30 of the total sample size were calculated using the G-power 3.1 software. However, a larger sample size was planned to be used in this trial due to repeated measurement. We used the GLIMMPSE software for repeated measurement calculation with the shoulder flexion range of motion as the main effect indicator that refers to the results of Başkaya et al. [25]. We choose a test power of 0.95 and a type 1 error rate of 0.05, 58 of sample size was calculated, considering 20% dropout rate, the actual total sample size is 70.

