### Randomization and blinding

Random number sequences are generated in the randomization software by an independent researcher; the 200,000 was used as the seed number to generate 70 random numbers. For avoiding tampering or transillumination, information of trial was written on the two layers of carbonless copy paper, which was placed in sealed, opaque, sequentially numbered envelopes. An independent research assistant will conduct the group allocation. Participants are required to write their name and admission number on the first layer of paper after disclosing the envelopes, random number sequence and group allocation can be seen only on the second layer of paper, and once the two layers of paper are separated, it cannot be restored. After participants sign the informed consent, the rater completes the baseline assessment, then the research assistant who is blinded to the study will perform the group allocation. Eligible participants will be randomly divided into either the MT group or the control group in a ratio of 1:1. After disclosing the envelope, the participant who obtains a paper marked with the number “1” will be allocated to the MT group, while the participant who obtains a paper marked with “2” will be grouped to the control group. Because of the nature of the intervention, rehabilitation therapists and nurses are not blinded, but they are not informed of the trial purpose; the rater, research assistant, and statistician are blinded, and they are also asked not to seek the group allocation and intervention from participants.

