### Data analysis

Data analysis will be processed by an independent statistician and primary researcher using the SPSS24.0 software. All statistical tests will be double sides; the statistical significance is set at *p* value < .05. Means and standard deviation or median and inter-quartile ranges will be calculated for continuous variables normally distributed and non-normally distributed, respectively. Categorical variables will be described as frequencies (*f*) and percentages (%). Demographics and other baseline values will be analyzed using the independent two-tailed *t*-test, non-parametric Mann-Whitney *U*-test, and chi-square test.

This study will adopt the modified intention-to-treat (mITT) principle. The effects of the intervention on primary and secondary outcomes (excluded arm circumference and incidence of lymphedema) between the groups will be analyzed by generalized estimating equation (GEE) from treatment, time points, and the interaction between group and time. Observed values of those outcomes at four assessments time points will be put into GEE, selecting the auto-correlation matrix and the robust standard error estimation method. Taking outcome index as the response variable, the group, time, and interaction of group and time will be incorporated into the model, in addition, selecting radiotherapy, the dominant hand, and type of surgery as covariates. The model includes the main effect and interaction effect, paired comparison variables will be selected, and the least significant difference (LSD) method will be used to adjust the multiple comparison effect. Arm circumference and incidence of lymphedema will be analyzed at each measurement time point between groups using the independent two-tailed *t*-test and chi-square test. In case of missing data, if missing data is completely random, the sample will not be included in the final data analysis. If missing data is incomplete random missing or non-random missing, multiple interpolations will be used to complete missing values.

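### The 20% dropout allowance multiplies 58 by 1.2 instead of dividing by 0.8, so 70 participants leave 56 rather than 58; the consequence for power is minor

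*Protocol article*

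**What the plan says.** The Sample size section of the protocol article reports two calculations. The first takes an "effect size value of 1.3799" from an earlier mirror-therapy trial and reports that "30 of the total sample size were calculated using the G-power 3.1 software". The second is a repeated-measures calculation in GLIMMPSE on shoulder flexion, with these settings: "We choose a test power of 0.95 and a type 1 error rate of 0.05". It ends: "58 of sample size was calculated, considering 20% dropout rate, the actual total sample size is 70".

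The total of 70 also appears in the Abstract and under Study design, and the Randomization and blinding section generates 70 random numbers. That section sets the allocation: "Eligible participants will be randomly divided into either the MT group or the control group in a ratio of 1:1". The Data analysis section makes the tests two-sided: "All statistical tests will be double sides". The article gives no other dropout rate and no inflation formula.

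**The concern.** The natural reading of the sentence is that 70 women are enrolled so that 58 remain after a fifth are lost, and that those 58 give 95% power. The three figures do not fit together in that way. Adding 20% of the number needed at the end is not the same as allowing for the loss of 20% of those who start, and the first always gives too few.

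What is at stake is the accuracy of the sample-size justification, which would otherwise pass into the results paper, where a reader can find the slip by hand. The number retained has some bearing on the analysis too, because the Data analysis section leaves participants out when their data are missing completely at random.

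**Working it through.** **Inputs.** From Sample size: required total 58, dropout 20%, stated total 70, power 0.95, type 1 error 0.05. From Randomization and blinding: 1:1 allocation. From Data analysis: two-sided tests.

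**Reproducing the plan's figures.**
- First calculation: a two-sided t-test with d = 1.3799 has power 0.954 at 15 per arm and 0.940 at 14 per arm. The total of 30 reproduces.
- The 58 cannot be rebuilt, because the means, standard deviations and correlations given to GLIMMPSE are not shown. It is taken as stated.
- The 70: 58 x (1 + 0.20) = 69.6, which rounds up to 70. This reproduces the stated total.

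**The allowance for a 20% loss among those enrolled.**
- Required enrolment = 58/(1 - 0.20) = 72.5, so 73. Equal arms need 74 (37 per arm).
- Check: 73 x 0.80 = 58.4 and 74 x 0.80 = 59.2, both at least 58.
- Rounding cannot turn 72.5 into 70.

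**What 70 delivers.**
- At 20% loss: 70 x 0.80 = 56, which is 58 - 56 = 2 short.
- Largest loss that still leaves 58: 1 - 58/70 = 0.171, about 17%.

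**Effect on power.** This step needs an assumption, since the GLIMMPSE inputs are missing. Simple tests stand in for the repeated-measures calculation.
- Suppose 58 (29 per arm) gives exactly 0.95. In a two-sided two-sample t-test the effect that does this is d = 0.963. With 56 (28 per arm), power is then 0.943.
- Other forms set to 0.95 at 58 give nearly the same at 56: normal approximation 0.943; F test with 2 degrees of freedom 0.942; F test with 3 degrees of freedom 0.942.
- Suppose instead that 58 is the smallest balanced total reaching 0.95, so its power may be a little higher than 0.95. The upper limit in the t-test is d = 0.981, at which 56 would itself reach 0.95 and 58 would give 0.956.
- Power at 56 therefore lies between about 0.942 and just under 0.95. Against the 0.95 target the loss is at most 0.950 - 0.942 = 0.008, or about 0.8 percentage points.

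**The case against.** The strongest reply is that this hardly matters. Two completers and less than one percentage point of power change no design decision, and multiplying by one plus the dropout rate is a common shortcut. That stands, and it sets the grade.

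A second reply is that the power figure belongs to the reviewer. The value d = 0.963 is nowhere in the article; it is solved backwards from 58 in a simpler test than the one GLIMMPSE ran. At the only effect size that the article states, 1.3799, a single-time-point t-test with 28 per arm would have power of about 99.9%. That is not the right model for the 58 either, but it shows how far the answer depends on the assumption. This reply also stands. Only a range can be given, and the exact value has to come from the original inputs.

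A third reply concerns missing data. A reader might infer that every woman with incomplete data is deleted, so that 56 is all the information left. The Data analysis section does not say that. It leaves participants out only where data are missing completely at random; otherwise it plans multiple imputation, and it fits a generalized estimating equation to the values observed at the four assessments. A woman lost after the 2-week or 4-week visit may therefore still contribute. The rule for completely random missingness does remove participants, so this reply weakens the point without disposing of it.

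Last, the article says only "considering 20% dropout rate" and does not promise in words that 58 will remain. That is fair as to the wording, but the article offers no other reading under which 70 follows from 58 and a 20% dropout rate.

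**Conclusion.** Wrong as written, minor severity. The arithmetic is certain given the stated 58, 20% and 70: the allowance was applied by multiplication, 70 leaves 56 at the stated dropout rate, and 70 secures 58 only up to about 17% loss.

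The effect on power is small and less certain: about 94% to just under 95% with 56 completers. This assumes that 58 is the smallest balanced total reaching 95%, that the loss is even across arms, and that simple tests are a fair stand-in for the repeated-measures calculation. The planned analysis may recover part of the loss.

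A reader might infer that the trial is underpowered or has to recruit more women. The documents do not support that: the shortfall appears only if dropout exceeds about 17%, and at the planned 20% it is two completers. Nor does this check show the 58 itself to be right or wrong, since its inputs are not given.

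**What to change.** Correct the sentence and leave enrolment at 70. Suggested text: *70 participants retain the required 58 if dropout is no more than about 17%; at 20% dropout 56 remain and power is slightly below 95%.* The sponsor should recompute the exact power at 56 from the original GLIMMPSE inputs before putting a figure in the text; the stand-in values above should not be copied in.

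The cost is one sentence, one rerun of an existing calculation, and a slightly less favourable statement of power or dropout allowance. Recruitment, the 70 random numbers and the analysis stay as they are.

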### Participants

#### Inclusion criteria

Women aged ≥ 18 years.Clinically diagnosed with breast cancer for the first time according to imaging examination and (or) pathological examination.The surgical treatment of breast includes modified radical mastectomy, mastectomy, or conservation surgery; the surgical treatment of the axilla is axillary lymph nodes dissection (ALND) or sentinel lymph node biopsy (SLNB).Having the ability to use social software such as WeChat.The signing of the informed consent form.

#### Exclusion criteria

Clinically diagnosed as bilateral breast cancer or cancer metastasis;With shoulder disease, upper limb fracture, neurological deficits, lymphangitis, and any injury of the upper limbsHaving suffered from severe cardiovascular disease, cognitive limitations, or mental diseaseHaving visual field defectReceiving immediate reconstruction in surgery

